## Methods

### Reform to the general medical services contract in England

The 2014/15 General Medical Services contract introduced a requirement for
general practices in England to offer patients aged 75 or over a named
accountable general practitioner, who should provide longitudinal continuity of
care within the general practice and be accountable for coordinating care to
meet the patient’s health and social care needs. In particular, the named
accountable general practitioner should ensure that patients receive all
appropriate services and work with relevant associated healthcare and social
care professionals to deliver a multidisciplinary care package [24,35]. The contract requires that the practice notify the patient of their
named accountable general practitioner, usually by letter, and make a reasonable
effort to accommodate patient preferences about the choice of general
practitioner. However, patients are not prevented from seeing any other general
practitioner in the practice [36]. The
2014/15 GMS contract changes led to a step change (discontinuity) in the
percentage of patients receiving a named accountable general practitioner, which
increases from around 5% to around 80% near age 75 (Table 1).

**Table 1 T1:** Preliminary analysis of data from Clinical Practice Research Datalink
showing that the requisite discontinuity exists in the data.

	Patients aged 70–74 (%)	Patients aged 75–79(%)

Notified of named accountable general practitioner	5420 (5%)	67,770 (80%)
Not notified of named accountable general practitioner	99,830 (95%)	17,161 (20%)
Total	105,250	84,931

*Note:* Based on preliminary analysis of Clinical
Practice Research Datalink data. Figures are illustrative as this
analysis was based on 2014 data and not all exclusion criteria were
applied.

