### Study cohorts

All general practices in England were mandated to participate in the policy. We
will examine data from the electronic medical record of a national sample of
general practices that participate in the UK-wide Clinical Practice Research
Datalink. This is a validated and widely used research database that contains
anonymised, person-level clinical data for all registered patients, linkable to
other data sources, such as death records from the Office for National
Statistics and Hospital Episode Statistics administrative data [38].

We will study all English general practices that have submitted data to Clinical
Practice Research Datalink for the full 2014/15 financial year, excluding
practices for which data are identified by Clinical Practice Research Datalink
as not being up to research standard or that did not give permission for data
linkage. This is expected to result in approximately 200 practices. Within these
practices, we will study registered patients born between 1929 and 1949, and
thus aged between 65 and 85 in 2014. Patients will be excluded if they have
missing year of birth or gender, deregistered within the study period or were
identified as at high risk and started admission avoidance care, as part of the
Avoiding Unplanned Admissions Enhanced Service. All patients on the Service
received named accountable general practitioners irrespective of their age,
meaning that a regression discontinuity design is not appropriate for these
patients.

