## Statistical methods

Our initial analysis (Table 1) suggests that
the proportion of patients receiving a named accountable general practitioner is
discontinuous at the threshold, but this will be confirmed on receipt of the data.
We will also confirm that, although we would expect a trend in certain covariates
across age, there are no discontinuities in these covariates at age 75. This
comparison will be done graphically and include all patients, regardless of actual
treatment assignment. We do not expect such discontinuities to occur, but if they do
exist, this would lead us to question the validity of our study design.

As mentioned previously, the proportion of patients receiving a named accountable
general practitioner is unlikely to jump from 0 to 100% at age 75. It will therefore
be appropriate to apply a fuzzy regression discontinuity design [31], by fitting four regression models. Two
models will relate the outcome to a polynomial function of age: one model will be
fitted for people whose age lies within the bandwidth below the threshold and the
other model for people within the bandwidth above the threshold. The final two
models have treatment assignment as their dependent variable rather than outcome.
All models will use ordinary least squares regression and include patients
irrespective of their actual treatment assignment. We will calculate the estimated
treatment effect as the difference between the predictions of the two outcome models
at age 75, divided by the difference between the predictions of the two treatment
models at age 75.

The analysis will have regard to the rounded nature of the running variable (i.e.
age), resulting from the use of year of birth rather than full date of birth. This
will exclude the use of very small bandwidths, and so we will use a larger interval
spanning several years and model any trend in the endpoints by age using parametric
approaches based on polynomial functions [42,43]. In the absence of
information on full date of birth, it will not be possible to establish for a given
patient born in 1939 what date they turned 75, and therefore which side of the
threshold the patient is at the index date. We will remove the risk of
misclassification by excluding all patients born in 1939 when fitting the regression
models and making a small extrapolation around age 75 [42]. A final consideration is that, when the running variable
is only observed at discrete points, discretisation bias can occur because a change

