in slope close to the cut-off might be mistaken for a treatment effect when in fact
it is due to the ‘natural’ change in outcomes with age. We will correct
for this bias using a method that is based on the moments of the age distribution
[42].

We will conduct a series of additional specification tests to check the validity of
the study design [31]. First, we will repeat
the estimation procedure at non-discontinuity points, to confirm a treatment effect
of zero. Second, we will confirm that the estimated treatment effect is not
sensitive to the choice of bandwidth or order of polynomial. Third, we will repeat
the analysis when including covariates in the regression models. Although it is not
necessary to include covariates in regression discontinuity analyses, including them
may improve precision [37,42].

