### Required sample size

We believe that a 5% change in the number of general practice contacts would
represent a meaningful difference to general practice workload, since this
represents approximately one extra appointment per working day for an average
general practitioner [46]. Assuming an
average of 5 general practitioner contacts per 6-month period in the absence of
a named accountable general practitioner [47], and a standard deviation of 6 contacts [47,48], we will need
24,212 patients in each treatment group, at 90% power and two-sided p-value of

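### The placebo test, as written, repeats the fuzzy ratio at ages where receipt of a named general practitioner does not jump, so it divides by about zero and says little about validity

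*Protocol article*

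**What the plan says.** Under Statistical methods, the article sets up a fuzzy regression discontinuity analysis "by fitting four regression models": two for the outcome and two for treatment receipt, one of each on either side of the threshold. It defines the "treatment effect as the difference between the predictions of the two outcome models" at 75, "divided by the difference between the predictions of the two treatment" models at the same age. No other estimator is defined.

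The same section then lists three further specification tests of the design's validity. The first is to repeat "the estimation procedure at non-discontinuity points, to confirm a treatment effect" of zero. The article does not say that the treatment models are dropped for this test, or that the denominator from age 75 is kept.

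The section on the contract reform locates the step in receipt: it "increases from around 5% to around 80% near age 75".

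**The concern.** A placebo test in a regression discontinuity study asks whether the fitted models produce a jump in the outcome where none should exist. It matters here because only year of birth is available. The 1939 cohort is left out, the models extrapolate to 75, and the article's limitations concede that the estimates depend on model specification. A placebo test on the outcome would show whether that extrapolation creates jumps by itself.

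A point with no discontinuity is one where receipt does not jump. Repeating the ratio there gives a denominator with expected value near zero. The estimate becomes unstable and its interval very wide. A non-significant result would then say almost nothing about whether the outcome jumped, yet it could be reported as support for the design.

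**Working it through.** The article gives no figure for the placebo test, so there is none to reproduce.

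**Inputs from the article**
- Receipt (Table 1): 5,420/105,250 = 5% at ages 70–74 and 67,770/84,931 = 80% at 75–79, a step of about 0.75.
- Patients per year of age: 105,250/5 = 21,050 below 75 and 84,931/5 = 16,986 above.
- SD 6 contacts and target 5% of 5 = 0.25 contacts (Required sample size). Diluted by the step in receipt, the target is 0.75 × 0.25 = 0.1875.
- Cohort: "thus aged between 65 and 85 in 2014".

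**Assumptions** (not fixed in the article): linear models, four single-year ages per side, cut-off year left out, placebo ages 70 and 80, receipt flat on each side of 75, yearly counts at 65–69 and 80–84 equal to those of the neighbouring Table 1 band, and independent errors in outcome and receipt.

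**1. Standard errors at placebo age 70.** With ages 1 to 4 years from the cut-off, the variance factor of the intercept is 1/4 + 2.5²/5 = 1.5 per side, so 3 for the difference.
- Outcome jump: 6 × √(3/21,050) = 0.072.
- Receipt jump: √(0.05 × 0.95 × 3/21,050) = 0.0026, around a true value of 0.

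**2. Size of the ratio with no outcome jump.** A ratio of two independent zero-mean normals is Cauchy, and its median absolute value is the ratio of the two SDs. Sample size and design factor cancel:
- below 75: 6/√(0.05 × 0.95) = 27.5 contacts;
- above 75: 6/√(0.8 × 0.2) = 15 contacts.

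**3. Ceiling on the Wald test.** For independent numerator and denominator, the delta method gives 1/t² = 1/t_num² + 1/t_den². So |t| cannot exceed |t_den|. Without a receipt jump, t_den is about standard normal, and rejection at the 5% level cannot exceed about 5%, however large the outcome jump. This does not depend on bandwidth or polynomial order, provided the treatment models fit and the window does not cross 75.

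**4. Simulated rejection rates** (20,000 runs each):

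| False outcome jump | Age 70: ratio | Age 70: outcome alone | Age 80: ratio | Age 80: outcome alone |
|---|---|---|---|---|
| 0 | 0.0% | 4.9% | 0.0% | 5.0% |
| 0.1 | 0.1% | 29% | 0.1% | 24% |
| 0.1875 | 0.8% | 75% | 0.6% | 66% |
| 0.25 | 1.6% | 94% | 1.3% | 88% |
| 0.5 | 4.0% | 100% | 3.8% | 100% |
| 1.0 | 4.5% | 100% | 4.6% | 100% |

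Hand check at 0.1875, age 70: 0.1875/0.0716 = 2.62, so power for the outcome jump alone is Φ(2.62 − 1.96) = 0.745, in line with the simulated 75%.

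**5. Real threshold.** At 75, with a denominator of about 0.75, the ratio test behaves properly: it rejects in 4.9% of runs with no jump and 91% with a 0.25 outcome jump.

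**6. Independence.** Repeating the calculation at age 70 with a correlation of 0.3 between the two errors raises rejection at 0.1875 from 0.8% to about 2%. At a jump of 1.0 it stays just under 5%.

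**The case against.** The best defence is that one condensed sentence is being read too literally. An expected effect of zero makes sense for the outcome jump, or for that jump scaled by the denominator at 75, but not for zero over zero. If the authors meant either, the test is sound. But neither reading is in the text. It names a procedure, and the only one defined includes the division. That makes it more than a detail left to a fuller plan.

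A second defence concerns inference. The article names no test for the ratio. With a Fieller or Anderson–Rubin test of zero effect, the statistic reduces to that of the outcome jump and the power returns. This stands as a limit. A reader might infer that the placebo test can never fail, but the ceiling of about 5% belongs to the Wald/delta-method test, which is an assumption here. It also loosens if the fitted receipt shows a spurious step: a step of 0.01 at age 70 brings rejection at 0.1875 up to about 57%, but only because the treatment model is itself misfitted.

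Third, a reader might infer that the test would return an estimate close to zero and so falsely reassure. It would not. Estimates of tens of contacts against an assumed mean of 5 would look broken. False comfort could come only from non-significance or a wide interval.

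Fourth, this is not the only or the first validity check. The graphical check for covariate jumps at 75 comes earlier in the same section, and those covariates include general practice contacts in the 6 months before the index date. That stands, though it is a visual check and does not test the study outcome.

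**Conclusion.** The point holds as a defect in the stated test. Followed as written, the placebo test divides by about zero. The ratio has a median absolute value of about 28 contacts below 75 and 15 above with no outcome jump at all. Under a Wald test it flags a false jump at most about 5% of the time, where the outcome jump alone would usually reveal one of the size that matters. It is uninformative in both directions.

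The ceiling rests on the Wald/delta-method test, independent errors and treatment models that fit within a window on one side of 75. The specific rates also rest on the assumed bandwidth, order, placebo ages and cell counts.

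A reader might go further and doubt the main result. The documents do not support that: the estimator at 75 has a large denominator and is not touched by this point.

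**What to change.** State in the specification tests that the placebo analyses use only the difference between the predictions of the two outcome models (the reduced form) at each placebo age. Add that the fitting windows lie wholly on one side of 75, so that the real step in receipt does not enter them. The cost is one sentence and less computing, since the two treatment models are not needed.

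Two additions would be useful but are not needed to cure the defect: a stated margin for judging the placebo jumps, for example 0.19 contacts (the diluted target), and the same outcome-jump test at 75 in a year before the policy, which would need one more year of the database.

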### Study endpoints and covariates

Our primary endpoint will be the number of general practitioner contacts per head
over 6 months; this will include all appointment types (e.g. both surgery visits
and telephone calls). Secondary endpoints, also calculated over 6 months, will
be a measure of longitudinal continuity of care; the number of contacts with
general practitioners or practice nurses; numbers of referrals to specialist
care; and number of common diagnostic tests (e.g. blood pressure). There are
several measures of longitudinal continuity of care, which focus on the
concentration, dispersion, distribution or sequence of consultations [12,17]. The Usual Provider of Care index measures the proportion of
contacts with the general practitioner who is most commonly seen [17]. The Usual Provider of Care index is
widely used [11] and is more easily
interpreted than some of the other measures [12]. The Usual Provider of Care index was not chosen as the primary
endpoint, as this measure is only defined for the subgroup of study participants
with at least two general practitioner contacts during the study period. The
theory behind the intervention is such that a change to the number of general
practitioner contacts, referrals to specialist care or numbers of diagnostic
tests is more likely following an improvement to continuity of care. However, we
will analyse these endpoints regardless of the findings for the Usual Provider
of Care index, since it is theoretically possible that, for example, the letters
led to an increase in enquiries from patients without improvements to
continuity.

The following covariates will be calculated for all patients, using data recorded
prior to the index date: gender; ethnicity; socioeconomic score (attributed to
the patient according to their area of residence, and measured by deciles of the
Index of Multiple Deprivation 2010) [40];
number of long-term health conditions recorded prior to the index date; and
numbers of general practice contacts, referrals to specialist care, diagnostic
tests and hospital discharges in the 6 months prior to the index date. Long-term
conditions will be defined in accordance with the Quality and Out-comes
Framework. The data quality for the Quality and Outcomes Framework indicators is
enhanced as a result of these conditions forming part of the pay-for-performance
scheme for general practice [41].

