0.05. Although the precise statistical power of the study will depend on the
bandwidth, the Clinical Practice Research Datalink database will provide more
than the required number of patients (Table 1) [37].

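### Prior contacts are calculated for every patient but kept out of the main model: a valid analysis that may give up precision, by an amount the article does not let us fix

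*Protocol article*

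**What the plan says.** All references are to the protocol article.

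- **Study endpoints and covariates.** The primary endpoint is general practitioner contacts per head over 6 months. The covariates calculated for all patients include "numbers of general practice contacts, referrals to specialist care, diagnostic" tests and hospital discharges over the 6 months before the index date, as well as gender and the number of long-term conditions.
- **Statistical methods.** The main estimator uses four least-squares models, two for outcome and two for treatment, fitted on either side of the threshold. The outcome models are described as polynomials in age, with no other term named. Patients born in 1939 are left out and the fits are extrapolated to age 75.
- **Statistical methods, specification tests.** The third test repeats "the analysis when including covariates in the regression models. Although it is not" and goes on to say that covariates are not required in this design but could sharpen the estimate.
- **Exposure variable and index dates.** For treated patients the index date is the day the named general practitioner was recorded, between April and September 2014. Other patients get a random date with the same monthly distribution. The bandwidth is left to cross-validation.
- **Required sample size.** The calculation assumes an "average of 5 general practitioner contacts per 6-month period in the absence of" a named general practitioner, "a standard deviation of 6 contacts" and a 5% change. It has no term for covariate adjustment.

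**The concern.** A patient's earlier contact count is a natural predictor of the later one. The article has a close version of it for everyone, acknowledges that covariates may help, and gives no reason for holding them back from the main estimate.

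Precision matters more here than in a plain two-group comparison. The estimator extrapolates two separately fitted curves to an age with no data and then divides by a treatment jump below 1. Both steps inflate the variance. The section on strengths and limitations presents the ability to detect a 5% change as one of four features that distinguish the study.

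**Working it through.** **1. The article's own sample size.** The effect is 5% of 5 = 0.25 contacts, with SD 6, two-sided alpha 0.05 and 90% power.

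n per group = 2 × (1.960 + 1.2816)² × 6² / 0.25² = 12,105 (12,106 with the t distribution). The t-based total for two groups is 24,212. The article states "24,212 patients in each treatment group", so its figure matches the total rather than one group. That is a separate matter. Here it shows only that the calculation is a simple two-group one with the unadjusted SD. Taken at face value, 24,212 per group gives 99.6% power for 0.25, or 93% for 0.25 × 0.75.

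**2. Inputs for the planned estimator.**
- Treatment jump from Table 1: 67,770/84,931 − 5,420/105,250 = 0.798 − 0.051 = 0.746, taken as 0.75. The detectable difference in outcome at 75 is 0.25 × 0.75 = 0.1875.
- Patients per year of age: 105,250/5 = 21,050 below and 84,931/5 = 16,986 above, held flat (assumption).
- Widest bandwidth: birth years 1929 to 1949 without 1939, so 10 years a side.
- First stage treated as known, with no allowance for practice clustering (assumptions).
- R-squared, the share of outcome variance removed by covariates: **not in the article**. Assumed 0.10, 0.25 and 0.49, which are correlations of about 0.3, 0.5 and 0.7.

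**3. Formula.** With m single-year ages at distances 1 to m from 75, the variance of the prediction at 75 is (SD² / patients per year) × k, where
- linear: k = 2(2m + 1) / [m(m − 1)]
- quadratic: k = 3(3m² + 3m + 2) / [m(m − 1)(m − 2)]

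Relative to a plain mean the inflation is m × k: 5.5 (linear, m = 5), 23 (quadratic, 5), 4.7 (linear, 10) and 13.8 (quadratic, 10).

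SE = √[36 × k × (1/21,050 + 1/16,986)]. Adjustment multiplies it by √(1 − R²). Power = Φ(0.1875/SE − 1.96).

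Example, linear with m = 5: k = 22/20 = 1.1, SE = 0.0649, 0.1875/0.0649 = 2.889, power = Φ(0.929) = 82%. At R² = 0.25, 2.889/√0.75 = 3.336 and power = 92%.

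**4. Results.**

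| Model | Unadjusted | R² 0.10 | R² 0.25 | R² 0.49 |
|---|---|---|---|---|
| Linear, 5 years a side | 82% | 86% | 92% | 98% |
| Linear, 10 years | 99% | >99% | >99% | >99% |
| Quadratic, 5 years | 29% | 32% | 37% | 51% |
| Quadratic, 10 years | 73% | 78% | 85% | 95% |

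The R² needed for 90% power is 1 − (0.1875/SE ÷ 3.2416)². That is 0.21 for linear at 5 years (ratio 2.889), 0.37 for quadratic at 10 years (ratio 2.576) and 0.81 for quadratic at 5 years (ratio 1.413). Linear at 10 years needs none. Linear at 6 years reaches 90% unadjusted (k = 26/30, SE = 0.0576, ratio 3.255).

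**5. Smaller effective samples.** Table 1 is labelled illustrative, with not all exclusions applied. At 75% of its counts, linear at 5 years goes from 71% unadjusted to 82% at R² 0.25. At half the counts, or with an assumed design effect of 2, it goes from 53% to 66%.

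**6. The look-back window.** For an index date late in September 2014, the preceding 6 months lie almost wholly after the policy began in April 2014. The covariate as defined can therefore be counted inside the policy period. This also touches the adjusted check already planned.

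**The case against.** The case for leaving the plan alone is strong on several counts, and most of it stands.

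- **No error is shown.** Regression discontinuity does not need covariates, and an unadjusted main analysis with an adjusted check is sound. The adjusted estimate will be produced in any case. A reader might infer that the main result would be biased without prior contacts; nothing in the article supports that.
- **The power claim does not rest on adjustment.** A reader might infer that the study needs this precision to reach its stated power. The sample-size section uses the unadjusted SD and is met on its own terms. For the real estimator, one more year a side in the linear model reaches 90% with no covariates, and in the 5-year quadratic even R² 0.49 falls far short. Adjustment decides the matter only between these cases.
- **Prognostic strength is assumed.** It is plausible that prior contacts predict later ones strongly, but the article gives no correlation.
- **The covariate is not the endpoint measured earlier.** The covariate is general practice contacts and the endpoint is general practitioner contacts. The article treats contacts with general practitioners alone and contacts with general practitioners or nurses as distinct endpoints, so the difference may lower the correlation.
- **There are larger threats to power.** The two-group formula ignores the extrapolation variance and the division by the treatment jump. Moving covariates corrects neither.

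What remains is narrower. The covariates and the adjusted analysis are already planned, so making that analysis primary is a cheap use of data in hand.

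**Conclusion.** The point holds as a missed efficiency, not as a flaw in validity. The main estimator omits baseline covariates that the plan already calculates and that the article concedes could help. Under the stated assumptions the gain from R² 0.25 is about 10 points of power for linear at 5 years, 12 for quadratic at 10 years, 8 for quadratic at 5 years and almost nothing for linear at 10 years. Which case applies is unknown until bandwidth and order are chosen, and the R² itself is an assumption. Flat counts by age, a known first stage and no clustering all make the absolute power figures optimistic. The covariate smoothness at 75 that adjustment relies on is already to be checked, though only graphically.

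**What to change.** Prespecify the covariate-adjusted fuzzy regression discontinuity as the primary analysis and the unadjusted version as a sensitivity analysis. State four things:

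1. **Covariates:** prior general practitioner contacts, number of long-term conditions and gender, all measured before the policy.
2. **Prior contacts:** count general practitioner contacts, to match the endpoint, in a fixed window ending before April 2014.
3. **Models:** use the same covariates in the outcome and the treatment models.
4. **Prediction at 75:** either hold covariate coefficients common across the threshold, or predict both sides at the same covariate values.

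**Cost:** a short paragraph, one re-derived variable and no new data source. The fixed window leaves a gap of up to about 6 months before follow-up, which may lower the correlation and so the gain. The unchanged estimand rests on the covariates being smooth at 75.
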